### Inclusion criteria

2.5

Children aged 1 to 5 years enrolled at the CREN in the city of Maceió whose parent/guardians signed as statement of informed consent agreeing to the participation of the children.

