**Methods::**

Mandatory inclusion criteria are diagnosis of malnutrition. The sample will consist of 50 men and women malnourished children aged 12 to 71 months. Saliva will be collected and the volume of saliva will be measured and the salivary flow rate will be determined (mL/min). Concentrations of salivary IgA in all samples will be measured using a commercial Enzyme-Linked Immunosorbent Assay (ELISA) kit. Low-level laser (laser diode) will be administered in the region of the parotid glands bilaterally as well as in the regions of the submandibular and sublingual glands.

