It is important to study the impact of malnutrition in children because its long-term consequences could be reduced which implies promoting positive effects on oral and general healthy.

The primary aim of this trial is to evaluate the effect of low-level laser on the saliva of children aged 1 to 5 years with energy-protein malnutrition. Secondary outcomes are to establish the degree of malnutrition in children aged 1 to 5 years and to analyze the saliva of children aged 1 to 5 years with energy-protein malnutrition.

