#### Characteristics and size

2.3.1

This cross-sectional study will use a sample of children aged 12 to 71 months of the 7th Administrative Region of Maceió. This region is one of the poorest region in Maceió. The children's parents/guardians will be interviewed at the CREN in the city of Maceió, state of Alagoas, Brazil. The sample size was estimated considering a prevalence of malnutrition of about 10% in children under 6 years old, with statistical power of 80% and 95% significance, resulting in a sample of 50 children.

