### Exclusion criteria

2.6

Children aged 1 to 5 years not enrolled at the CREN in the city of Maceió and children whose parents/guardians did not sign a statement of informed consent, teachers, caregivers, health professionals, and voluntary interns.

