#### Evaluation of nutritional status

2.7.1

The children will be weighed on a duly calibrated electronic anthropometric scale (capacity: 150 kg; precision: 100 g) barefoot and wearing light clothing in the presence of the mother or caregiver. Height will be determined using a non-flexible metric tape measuring 2 m in length (precision: 0.1 cm). The measurement will be performed twice and the mean will be used for the calculation of the indices. Using these measures, height for age and weight for age will be determined using the nutritional reference standards recommended by the World Health Organization, with a cutoff point (*Z* score) between +1 and –1 standard deviations (SD) of the median indicative of the ideal range, *Z* between –1 and –2 SD indicatives of mild malnutrition, *Z* between –2 and –3 SD indicatives of moderate malnutrition and *Z* >–3 indicative of severe malnutrition.^[29]^

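### Malnutrition is a mandatory entry criterion in the abstract but absent from the eligibility sections, so currently well-nourished children can be enrolled, irradiated and counted

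*Protocol article*

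**What the plan says.** The protocol article describes the study population in several places.

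- **Abstract, Methods:** "Mandatory inclusion criteria are diagnosis of malnutrition", followed by "The sample will consist of 50 men and women malnourished children aged 12 to 71 months".
- **Background, primary aim:** to "evaluate the effect of low-level laser on the saliva of children aged 1 to 5 years with energy-protein malnutrition".
- **Section 2.3.1:** "This cross-sectional study will use a sample of children aged 12 to 71 months of the 7th Administrative Region of Maceió". No nutritional condition is attached. The size of 50 is said to follow from a malnutrition prevalence of about 10% in children under 6.
- **Section 2.5, inclusion:** "Children aged 1 to 5 years enrolled at the CREN in the city of Maceió whose parent/guardians signed as statement of informed consent".
- **Section 2.6, exclusion:** "Children aged 1 to 5 years not enrolled at the CREN in the city of Maceió and children whose parents/guardians did not sign" a consent form, together with adult staff and volunteers.
- **Section 2.7.1, under Interventions:** weight and height are converted to height-for-age and weight-for-age Z scores and graded. The top class is "between +1 and –1 standard deviations (SD) of the median indicative of the ideal range"; mild, moderate and severe malnutrition follow. No class is named as a condition of entry.
- **Section 2.9:** salivary flow and IgA are compared before and after laser and correlated with malnutrition. No subgroup is singled out for the comparison.

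**The concern.** Eligibility decides which children the result describes. The abstract and the aim say malnourished children; the sections that govern enrolment say any consenting CREN child of the right age. Two investigators, one following the abstract and one following section 2.5, could recruit different samples.

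Two things are at stake. The before/after change may be averaged over children outside the stated target group, which blurs its meaning and, if they respond less, weakens the test. And young children who do not have the condition named in the aim could receive laser without the document saying that this is intended.

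**Working it through.** **Step 1: the texts side by side.** Take a consenting child enrolled at CREN, aged 3, with Z = 0 on both indices.

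| Place | Does this child qualify? |
|---|---|
| Abstract, Methods | No: malnutrition is mandatory |
| Primary aim | No: outside the target population |
| 2.5 Inclusion | Yes: age, enrolment and consent are met |
| 2.6 Exclusion | Not excluded |
| 2.7.1 Nutritional status | Graded in the top class; no consequence stated |
| 2.9 Laser and comparison | Treated and compared before and after |

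The abstract and aim give one answer and the operative sections the other. Nothing elsewhere settles it.

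**Step 2: the stated sample size.** Inputs from section 2.3.1: p = 0.10, power 80%, 95% significance (read as two-sided alpha 0.05), N = 50. The precision formula n = 1.96² × p(1 − p) / d² gives 139 at d = 0.05, 55 at d = 0.08 and 35 at d = 0.10. It returns 50 only at d of about 0.083, which is not stated. Without a stated precision or alternative, 50 can be neither confirmed nor refuted. The point does not depend on it.

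**Step 3: what dilution could cost (illustration only).** The assumptions below are not in the document:
- a paired before/after test in 50 children, two-sided alpha 0.05, normal approximation;
- 80% power if all 50 are malnourished;
- no effect in well-nourished children;
- the SD of the change is unaffected by mixing.

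The standardised change giving 80% power is (1.960 + 0.842) / √50 = 0.396. If a share m is malnourished, the mean change becomes m × 0.396, and power = Φ(m × 0.396 × √50 − 1.960) = Φ(m × 2.802 − 1.960).

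| Share malnourished | m × 2.802 − 1.960 | Power | Children to enrol for 50 malnourished (50/m) |
|---|---|---|---|
| 100% | 0.842 | 80% | 50 |
| 90% | 0.561 | 71% | 56 |
| 75% | 0.141 | 56% | 67 |
| 50% | −0.559 | 29% | 100 |

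The document gives no share for CREN enrollees, so none of these rows can be picked as the likely one.

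**The case against.** The best reply is that the site is a nutrition-recovery centre, so enrolment there may itself imply malnutrition and section 2.5 may carry the criterion tacitly. That is plausible and may make the practical effect small. It does not remove the conflict. No admission criterion is given, the centre also has an educational role, section 2.4 refers to registration by learning class, and a recovery centre may hold children who have already recovered. Even if every child was malnourished on admission, the index, cut-off and date that make a child eligible would still be open.

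It can also be said that a full reference scale with a normal class is no evidence that normal children are wanted, and that grading nutrition is itself a secondary aim. Both are fair; the scale only shows that no threshold was set. Likewise, the regional frame and CREN enrolment may be nested, since parents are interviewed at CREN. That is a matter to clarify, not a proven contradiction.

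Two stronger readings are tempting and should not be drawn.

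- A reader might apply the 10% prevalence to the sample and infer that only about 50 × 0.10 = 5 children would be malnourished, then set what is detectable in 5 against what is detectable in 50. The 10% is a general figure for children under 6, not the share among enrollees of a recovery centre. Moreover, all 50 would be analysed, so the harm is a diluted effect and not an analysis of 5.
- A reader might assume that well-nourished enrollees have healthy salivary glands. The Background says that gland function can stay depressed long after early malnutrition, so a recovered child may still be affected. The no-effect assumption in the illustration is therefore the unfavourable end.

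**Conclusion.** The contradiction stands and is certain from the text: a criterion called mandatory in the abstract is missing from the sections that govern enrolment, and the before/after comparison does not restore it. Currently well-nourished children can therefore be enrolled, irradiated and counted.

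How many would be is unknown, and so is the loss. The powers of 71%, 56% and 29% rest on assumed shares of 90%, 75% and 50%, on no effect in well-nourished children and on an unchanged SD; they show sensitivity and are not a forecast. The document names no formal primary analysis set, so the comparison meant here is the before/after one that serves the primary aim.

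**What to change.** 1. Reconcile section 2.5 with the abstract by adding malnutrition at the baseline measurement as an inclusion criterion. The sponsor should state the index (height-for-age, weight-for-age, or how the two combine) and the Z cut-off, including whether mild malnutrition qualifies; the document decides neither.
2. Before citing the section 2.7.1 classes, correct the printed definition of severe malnutrition. It reads as Z greater than –3, which taken literally takes in children in the normal class.
3. Carry out the planned anthropometry before the first laser session, as an entry check.
4. State that only children meeting the criterion count towards the 50 and enter the main before/after comparison. Describe any others separately.
5. State in section 2.3.1 how the 7th Administrative Region relates to CREN enrolment.

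Weight and height are already to be measured, so the cost is mainly wording. Somewhat more children may need screening: 56, 67 or 100 to reach 50 at the illustrative shares of 90%, 75% or 50%. If CREN admits only children who meet the criterion, and they still meet it at baseline, no extra screening is needed.

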### Exclusion criteria

2.6

Children aged 1 to 5 years not enrolled at the CREN in the city of Maceió and children whose parents/guardians did not sign a statement of informed consent, teachers, caregivers, health professionals, and voluntary interns.

### Interventions

2.7

#### Evaluation of nutritional status

2.7.1

The children will be weighed on a duly calibrated electronic anthropometric scale (capacity: 150 kg; precision: 100 g) barefoot and wearing light clothing in the presence of the mother or caregiver. Height will be determined using a non-flexible metric tape measuring 2 m in length (precision: 0.1 cm). The measurement will be performed twice and the mean will be used for the calculation of the indices. Using these measures, height for age and weight for age will be determined using the nutritional reference standards recommended by the World Health Organization, with a cutoff point (*Z* score) between +1 and –1 standard deviations (SD) of the median indicative of the ideal range, *Z* between –1 and –2 SD indicatives of mild malnutrition, *Z* between –2 and –3 SD indicatives of moderate malnutrition and *Z* >–3 indicative of severe malnutrition.^[29]^

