### Administration of low level laser

2.9

Low-level laser will be administered using the Photon Lase III device (DMC Equipamentos LTDA, São Paulo, Brazil). Laser will be administered for 10 seconds on 4 intraoral points and 4 extraoral points in the region of the parotid glands bilaterally as well as 1 intraoral point and 1 extraoral point in the regions of the submandibular and sublingual glands. The first session will occur after the collection of saliva. The second and third sessions will be performed 7 and 14 days after the first session, respectively. The final saliva collection will be performed after the third laser session.^[34,35]^

The laser will be adjusted according to the following parameters: Central wavelength (nm) = 808; spectral band width (FWHM) (nm) = 2; operational mode = continuous; mean radiant power (mW) = 100; polarization = randomized; aperture diameter (cm) = 0.2; irradiation at aperture (mW/cm^2^) = 2500; beam profile = multimodal; beam spot on target (cm^2^) = 0.04; irradiation at target (mW/cm^2^) = 2500; exposure time (s) = 40; Radiant exposure (J/cm^2^) = 100.0; radiant energy (J) = 4; number of points irradiated = 10; irradiated area (cm^2^) = 0.40; application method = Contact; number of treatment sessions = 3; frequency of treatment sessions per week = 1; Total radiant energy (J) = 40.

The salivary flow rate and salivary IgA will be compared before and after of each laser application (after 7 and 14 days) and correlation with the malnutrition will be established. The results will be analyzed using ANOVA and Tukey's contrast test. The level of significance will be 5%.

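### The cutoff for severe malnutrition is printed with its inequality reversed, so it contradicts the other bands in the same sentence and leaves children below −3 SD without a class

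*Protocol article*

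**What the plan says.** Section 2.7.1 (Evaluation of nutritional status) of the protocol article derives height for age and weight for age against an international reference and grades the Z score in four steps:

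- Ideal: "between +1 and –1 standard deviations (SD) of the median indicative of the ideal range".
- Mild: "between –1 and –2 SD indicatives of mild malnutrition".
- Moderate: "between –2 and –3 SD indicatives of moderate malnutrition".
- Severe: the sentence closes with "indicatives of moderate malnutrition and *Z* >–3 indicative of severe malnutrition".

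No other section restates or corrects the severe cutoff.

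The grading serves one stated purpose and possibly a second. Section 1 (Background) says "Secondary outcomes are to establish the degree of malnutrition in children aged 1 to 5 years". Section 2.9 (Administration of low level laser) says of salivary flow and IgA that "correlation with the malnutrition will be established", without saying whether malnutrition enters as a grade or as a Z score. Section 2.8 (Saliva collection and analysis) names Pearson's correlation among the methods.

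**The concern.** The first three bands move down from the reference median, so the fourth should be the tail beyond moderate. The printed inequality points back up the scale instead. It takes in the three bands already defined and excludes the children furthest below the median, who are the ones a severe class exists to identify.

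At stake is a named secondary outcome with no other definition in the document. If the rule were coded as printed, children would carry two labels and the worst-nourished would carry none. The same fault would pass into the correlation with malnutrition if the grade is the variable used there. A reader who reuses the published definition would copy it.

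**Working it through.** No sample size or power figure lies behind this point, so there is nothing of the plan's to reproduce. The check applies the four printed rules literally to test values.

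**Inputs** (all from section 2.7.1): ideal −1 ≤ Z ≤ +1; mild −2 ≤ Z ≤ −1; moderate −3 ≤ Z ≤ −2; severe Z > −3. The text does not say which band owns a shared endpoint, so both ends are taken as included.

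| Z | Labels as printed | Labels if severe is Z < −3 |
|---|---|---|
| +2 | severe only | none (above the ideal range) |
| +0.5, 0, −0.5 | ideal and severe | ideal |
| −1.5 | mild and severe | mild |
| −2.5 | moderate and severe | moderate |
| −3 exactly | moderate | moderate |
| −3.5, −4 | none | severe |

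As printed, the ideal and mild bands lie wholly inside Z > −3. So does the moderate band, apart from the single point −3. Nothing covers Z < −3. With the inequality turned round, the mild, moderate and severe bands are contiguous, leave no gap below −1, and meet only at shared endpoints.

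**Size in the reference population.** For a standard normal Z, P(Z > −3) = 99.87% and P(Z < −3) = 0.13%. The printed severe rule therefore describes almost the whole reference population.

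**Size in the trial.** Section 2.3.1 gives the sample: "resulting in a sample of 50 children". The document gives no mean or SD of Z, so both are assumed here: normal, SD 1, mean m from −1 to −2.5. With Φ the standard normal distribution function:

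- number meeting the printed severe rule = 50 × [1 − Φ(−3 − m)]
- number with no class = 50 × Φ(−3 − m)

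| Assumed mean m | Φ(−3 − m) | Meet printed severe rule | No class |
|---|---|---|---|
| −1.0 | 0.0228 | 48.9 | 1.1 |
| −1.5 | 0.0668 | 46.7 | 3.3 |
| −2.0 | 0.1587 | 42.1 | 7.9 |
| −2.5 | 0.3085 | 34.6 | 15.4 |

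So about 49 down to 35 of 50 children would meet the printed severe rule, and about 1 up to 15 would have no class. These counts show scale only. The contradiction itself needs no distributional assumption.

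**The case against.** The best defence is that the intent is plain. The scale descends in order and is tied to a cited reference standard. The one reading that fits is more than 3 SD below the median, with the sign written loosely. Staff who know the standard would probably grade correctly, so misclassification in practice is not certain. That stands, and it limits the severity. It does not remove the point: the rule is stated in the Methods, it is wrong as stated, and nothing elsewhere in the document corrects it.

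Four stronger readings are tempting, and the document does not support them.

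- A reader might infer that the grading is worthless as written. It is not. The ideal, mild and moderate limits are coherent, and even the literal rules give each range a distinct set of labels: ideal with severe, mild with severe, moderate with severe, and none below −3. The fault lies in the severe label.
- A reader might infer that every analysis involving malnutrition is wrong. Section 2.9 does not say that the correlation uses the grade, and Pearson's correlation is ordinarily run on a continuous measure. If Z itself is used, the reversed sign does no harm there. The before/after comparison of flow and IgA by ANOVA does not use the cutoff.
- A reader might infer that eligibility is compromised, since the abstract requires a diagnosis of malnutrition. Section 2.5 (Inclusion criteria) sets no Z threshold, and the abstract does not tie the diagnosis to this scale.
- A reader might add that the text does not say which of the two indices sets the degree when they differ. Reporting each separately is compatible with what is written, and an article may leave such detail to the full protocol. It is not counted here.

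**Conclusion.** The point holds as a wrong definition of limited reach. The severe cutoff contradicts the other bands in its own sentence: it overlaps all three and leaves Z below −3 without a class. That follows from the printed inequalities alone.

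The exposure is the secondary outcome on degree of malnutrition. It extends to the correlation with malnutrition only if the grade is the variable used, which the document leaves open. The primary before/after comparison of saliva is unaffected. How many children would actually be misgraded cannot be known from the document. The range of about 1 to 15 unclassed children out of 50 rests on an assumed normal distribution with SD 1 and mean Z between −1 and −2.5, and on staff applying the rule literally.

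**What to change.** In section 2.7.1, reconcile the severe cutoff with the plan's own scale and with the reference standard it cites, so that severe is the band beyond moderate: Z < −3 in place of the printed inequality. In the same edit, assign each shared endpoint (−1, −2 and −3) to one band, so that no child on a boundary falls in two.

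Optionally, state that the Pearson correlation uses the continuous Z score. That analysis would then not depend on the grade. This is an improvement, and the error does not require it.

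The cost is one line of text, or two with the option. The Z scores are already planned, so no new measurement is needed and the sample size does not change. The correction should be in place before any child's grade is recorded or analysed. Grades already assigned can be rederived from the stored Z scores.

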### Saliva collection and analysis

2.8

Saliva will be collected at the dental sector of the CREN in the city of Maceió with the child seated in a dental chair under conventional light. Total resting saliva will be collected between 9 and 11 am (to avoid the influence of circadian rhythm) using the drainage method. The children will have not ingested food or beverages (except water) 1 hour before the procedure and will not have performed oral hygiene within 2 hours before the procedure. The child will be instructed to swallow prior to the collection and then instructed not to swallow, allowing the saliva to drain between the lips (which will be separated) into a test tube (aspirator) connected to a 15-mL Flacon tube positioned near the mouth.^[30]^ Collection time will be 5 minutes. The volume of saliva will be measured and the salivary flow rate will be determined (mL/min). Salivary flow values will be analyzed based on the values below^[31]^ (Table 1).

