**Table 1 T1:**
[figure not shown]
Salivary flow values for resting saliva (mL/min).

One aliquot (1 mL) of saliva will be transferred immediately to a small tube (capacity: 5 mL) for titration with hydrochloric acid 0.005 Ne. The tube will be shaken for 15 seconds and buffering capacity will be measured using a glass electrode (Orion) coupled to a pH meter (Procyon 720 A, Procyon, São Paulo, Brazil). Titration under partial carbon dioxide gas is considered the standard method for determining the buffering capacity of saliva. The reading of this test is performed based on the following parameters: pH 3.0 to 4.0 = very low to low buffering capacity; pH 4.5 to 5.0 = intermediate buffering capacity; and pH ≥5.5 = normal/good buffering capacity.^[32]^

The remaining saliva will be stored in Eppendorf tubes and frozen at –20 °C until the analysis of salivary IgA. Concentrations of salivary IgA in all samples will be measured using a commercial Enzyme-Linked Immunosorbent Assay (ELISA) kit (Diametra IgA Saliva Kit, Italy) (Fig. 1). Salivary IgA (μg/mL) in each sample will be calculated using a standard curve obtained from the calibrators in the kit^[19]^ and will be analyzed^[33]^ (Table 2).

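### Saliva collections share a common morning window but are not matched within a child, which adds modest, cheaply avoidable noise to the before/after laser comparison

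*Protocol article*

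**What the plan says.** Section 2.8 of the protocol article lays down one collection procedure and exempts no visit from it.

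- Clock time: "Total resting saliva will be collected between 9 and 11 am (to avoid the influence of circadian rhythm) using the drainage method".
- Fast and water: "The children will have not ingested food or beverages (except water) 1 hour before the procedure". This is a minimum with no upper limit, and water has no cut-off.
- Oral hygiene: the child "will not have performed oral hygiene within 2 hours before the procedure".
- Setting: "with the child seated in a dental chair under conventional light".
- Clearing the mouth: "The child will be instructed to swallow prior to the collection and then instructed not to swallow".
- Duration: "Collection time will be 5 minutes".

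Section 2.9 places the baseline collection before the first laser session and the final collection after the third, which falls 14 days after the first. It does not state the interval between the third session and the final sample. The comparison is: "The salivary flow rate and salivary IgA will be compared before and after of each laser application (after 7 and 14 days". No untreated or sham group is described. Nothing in 2.8 or 2.9 ties a child's later collection to the clock time, meal interval or water intake of that child's own baseline.

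**The concern.** The stated purpose of the window is to remove the circadian influence. A common window serves well for comparing children with one another. The laser question, however, rests on the change within a child between days, and there the window only caps the time difference at 2 hours. Time since the last meal can also differ between a child's samples, because the fast is only a minimum.

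Water bears directly on both outcomes. Flow is the volume collected in a fixed time, and IgA is a concentration, so water left in the mouth would raise the first and lower the second. The prior swallow reduces this, but it relies on children aged from 12 months (section 2.3.1) following an instruction.

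Two things could be at stake: precision, because unmatched conditions inflate the variance of the change, and bias, because without a concurrent comparison a consistent difference between visits would be counted as a laser effect. The two need separate checks.

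**Working it through.** The plan gives no figure for diurnal drift, meal effect, retained water or SD of change, so there is no stated figure to reproduce here.

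**Inputs from the article:** a 2-hour window (2.8); 50 children (2.3.1); 5% level (2.9), taken as two-sided; 10 irradiated points, with both 10 s and 40 s given as the time per point (2.9).

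**Assumptions:** slots are spread evenly over the window and independent between visits; flow or IgA drifts 5-15% of its mean per hour; the SD of the within-child change, with times matched, is 30-40% of the mean.

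**Step 1: clock gap within a child.** Let D be the difference of two independent uniform times on 2 hours.
- Mean of D = 0.
- Variance = 2 × 2²/12 = 0.667, so SD = 0.816 h (49 min).
- Mean absolute gap = 2/3 h = 40 min.
- P(gap over 1 h) = (1 − 1/2)² = 0.25.
- Standard error of the mean gap over 50 children = 49/√50 = about 7 min.

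**Step 2: added variance.** Noise SD = drift × 0.816. Variance ratio = 1 + (noise SD / SD of change)².

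| Drift per hour | Noise SD | Ratio, SD of change 40% | Ratio, SD of change 30% |
|---|---|---|---|
| 5% | 4.1% | 1.01 | 1.02 |
| 10% | 8.2% | 1.04 | 1.07 |
| 15% | 12.2% | 1.09 | 1.17 |

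The increase is therefore about 1-17%. At the top of the range, 50 unmatched children carry the information of 50/1.17 = about 43 matched ones; at the bottom, 50/1.01 = about 49.5.

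**Step 3: power and type I error.** Drift divided by SD of change runs from 5/40 = 0.125 to 15/30 = 0.5 SD per hour. For an effect detectable with 80% power when times are matched, power with unmatched times is 79.7%, 79.0%, 77.7% and 73.7% at slopes of 0.1, 0.2, 0.3 and 0.5 SD per hour. In a simulated paired t test (50 children, within-child correlation 0.5) with no true effect, the rejection rate over these slopes was 0.047-0.051, which is the nominal level.

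**Step 4: bias.** Bias = drift × mean gap. With independent slots the mean gap is zero, so the bias is zero. The one order difference built into the plan is that laser precedes the final sample but not the baseline. Irradiation alone takes 10 × 10 = 100 s to 10 × 40 = 400 s. At 400 s (0.11 h) the shift is 0.11 × 5-15% = about 0.6-1.7% of the mean, and the simulated type I error was 0.051-0.065. The waiting time after the third session is not stated, so irradiation time is not an upper bound on this shift.

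**Step 5: water.** The direction is clear (flow up, IgA down), but the volume retained after swallowing is unknown. The same water rule and the same swallow apply at every collection. If retention is similar at both visits, it cancels in the change in flow, and nearly so in IgA when saliva volumes are similar. Only a consistent difference in intake between visits would bias the change.

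**The case against.** The strongest reply is that section 2.8 already names the circadian threat and deals with it, and also fixes the oral hygiene interval, setting, prior swallow, method and duration for every visit. On this view the stated purpose of the window is loose wording for limiting the influence, and matching to the minute is operating detail that a condensed article may leave to the full protocol. The schedule figure is not visible either. An SD of change taken from ordinary visits would already contain such timing variation, so adding it again could double count.

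Much of this stands. The procedure is reasonably standardised, and the 17% figure sits in the extreme corner of the assumptions. What remains is that the article itself sets the timing and water rules in some detail, and as written they allow a 2-hour gap and water up to the moment of collection in a comparison that is purely within child.

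A reader might go further and infer that collection conditions will produce a false laser effect, or that retained water materially distorts flow and IgA. The document does not support either. A raised false-positive rate needs a systematic shift in clock time, and no passage sets up a large one; any rate quoted would only restate the shift assumed. An error in a single sample from an assumed water volume is not an error in the change.

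**Conclusion.** The point holds as a cheap improvement to a stated rule, not as a demonstrated error. Unmatched collection times leave an average gap of 40 minutes between a child's samples and raise the variance of the change by about 1-17%. This rests on independent, evenly spread slots, a drift of 5-15% per hour and a matched SD of change of 30-40%, none of which the document supplies. The power cost is from under 1 to about 6 percentage points, and type I error stays at about 5%.

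Bias arises only if timing, meal interval or water intake moves in one direction between visits. The sole directional feature in the plan is that the final sample follows laser. Irradiation time alone makes this small, but the interval to collection is open. The absence of an untreated group means that any such shift would go uncorrected. That is a wider design weakness, and matching collection conditions would not cure it.

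**What to change.** In section 2.8, keep the 9 to 11 am window and add:

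1. Each child's later collections are scheduled at about the same clock time as that child's baseline, for example within 15 minutes, and at a similar interval since the last meal.
2. The same short no-water interval applies before every collection, in place of the open exemption for water.
3. The clock time of each collection is recorded, and the mean within-child time difference is reported beside the before/after result.

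The cost is two or three sentences, one recorded time per sample and slightly less freedom in booking children within the morning. No extra children, visits or assays are needed. The change should be made before collection starts, because unrecorded times cannot be recovered later. It does not replace a control group.
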